### **6.2 Analysis of the Primary Outcome Measure (Reference: Protocol p. 20)**

All analyses will be conducted under the principle of intention to treat; all participants will be analyzed as members of the groups to which they were originally randomized to. We will examine the impact of the psychoeducation program on alcohol use, measured from baseline to twelve months, taking into account correlations within individuals, using multivariate mixed-effects models.

Our primary outcome variables will be initiation and escalation of substance use. Initiation of use will be defined as any new use of substances at follow-up among those reporting no past-12-month use at baseline. For alcohol use, escalation will be defined as, among drinkers, any increase in number of drinks (measured by TLFB) from baseline to follow-up. For marijuana use, escalation will be defined as, among users, any increase in days of smoking marijuana (measured by TLFB) from baseline to follow-up.

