### **6.0 OUTCOME ANALYSIS**

### **6.1 Definition of Primary Outcome Measure (Reference: Protocol p. 20)**

We will assess the magnitude and direction of the effects of hypothesized predictors on substance use. Specifically, we will examine the association between each factor and past year substance use, past 90 days use and number of drinks measured by TLFB. Multivariate logistic/linear regression, adjusting for demographic characteristics, will be performed.

To evaluate the effect of intervention on substance use at 6- and 12-month follow-up, we will perform multivariate logistic regression adjusting for demographics, predictors of substance use and baseline knowledge. Separate models will be used to evaluate effects at 6- and 12-month. Adjusted odds ratios will be computed for comparison between intervention and control groups.

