## **8.0 SIGNIFICANCE TESTING**

Statistical significance will be considered at  $p < .05$  for each analysis.

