## **11.0 UPDATES TO STATISTICAL ANALYSIS**

### **Updates in relation to 6.0 OUTCOME ANALYSIS**

Updated Date: 11/15/2016

The randomization checklist includes stratification by age and gender at each site. Within each stratum, treatment assignments will be randomly generated and assigned.

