#### **Defining Outcomes**

Primary Outcome(s): Past 3-month alcohol use measured by a Brief Frequency variable for alcohol use.

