#### **Data Analysis Approach**

The impact of the psychoeducation program on alcohol use, measured from baseline to twelve months, taking into account correlations within individuals, using multivariate mixed-effects models adjusting for baseline characteristics.

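### The SAP does not fix one primary outcome, model or deciding contrast: sections 6.1, 6.2 and 9.0 were never reconciled with the section 11.0 updates, and no multiplicity rule is given.

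*Supplement*

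**What the plan says.** **Outcome.** SAP 6.2 states: "Our primary outcome variables will be initiation and escalation of substance use". It defines initiation for substances in general, and escalation separately for alcohol (number of drinks) and marijuana (days of use). SAP 2.1.1 repeats this and states one hypothesis per substance, each at 6 and 12 months. The update to section 6.0 dated 6/27/2019, in SAP 11.0, gives the primary outcome as "Past 3-month alcohol use measured by a Brief Frequency variable for alcohol use".

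**Model.** SAP 6.1 plans adjusted logistic regression: "Separate models will be used to evaluate effects at 6- and 12-month". SAP 6.2 plans a mixed-effects model of alcohol use from baseline to twelve months. The update of 12/16/2020 repeats that model, "using multivariate mixed-effects models adjusting for baseline characteristics". Neither mixed-model text says which treatment contrast decides the trial.

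**Error rate.** SAP 8.0 sets the threshold at p<.05 "for each analysis". It states no sidedness, hierarchy or adjustment.

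**Power.** SAP 9.0 is still written for participants who initiate or escalate substance use, with adjusted odds ratios of 2.0 or more.

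**Randomisation.** The update of 11/15/2016 says: "The randomization checklist includes stratification by age and gender at each site".

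**The concern.** A confirmatory trial needs one outcome, one model and one contrast fixed in advance. Here the latest SAP gives two descriptions of the primary analysis and does not say which prevails. An analyst who follows 6.1 and the definitions in 6.2 would fit several logistic models, by substance, type of change and month. An analyst who follows 11.0 would fit one longitudinal model of alcohol use. Under SAP 8.0 either could report any result below .05 as a primary finding.

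The body is not simply old text left above a list of updates. Section 6.2 already carries the mixed-model sentence of the 2020 update. The abbreviation list already contains HTE and TGC, which belong to the 9/28/2023 entry. So the body was revised at least in part and still keeps initiation and escalation as primary. This is a contradiction inside the current SAP, not a difference between versions.

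**Working it through.** **Plan's own figures.** The SAP states no family-wise error rate, so there is none to reproduce. Its one related figure is the power claim in 9.0: 300 completers, power .80, odds ratio 2.0, intervention-arm prevalence .20 to .55. Allocation is not stated; 1:1 (150 per arm) is assumed. A comparison of two proportions then gives:

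- two-sided .05: power .745 at prevalence .20 (344 participants needed for .80), .847 at .40 and .820 at .55;
- one-sided .05: power .836 at .20 and .911 at .40, with 300 needed at .20 once a continuity correction is applied.

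The claim therefore holds over the whole stated range only if one-sided. This does not affect the error rates below, but it shows that 9.0 should state sidedness. In any case it concerns initiation or escalation, not the 2019 outcome.

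**Inputs for the error rate.**
- Per-test level: .05 (SAP 8.0). Two-sided is assumed.
- Number of primary tests k: depends on which text is followed.

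**Formula.** For k independent tests with no true effect, the chance of at least one false claim is 1 − .95^k.

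| Reading | Tests | k | Chance of at least one false claim |
|---|---|---|---|
| Updates govern | one treatment contrast from the mixed model | 1 | 5.0% |
| Updates govern, both months tested | 2 contrasts | 2 | 1 − .95² = 9.75% |
| Body, as hypothesised in 2.1.1 | (initiate or escalate) × 2 substances × 2 months | 4 | 1 − .95⁴ = 18.5% |
| Body, 6.2 definitions read literally | (initiation once, escalation twice) × 2 months | 6 | 1 − .95⁶ = 26.5% |
| Body, fully split | (initiation, escalation) × 2 substances × 2 months | 8 | 1 − .95⁸ = 33.7% |

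**Correlation.** The same participants contribute at both months and for both substances, so the tests are not independent. The documents give no correlations. In simulation of normal test statistics, with correlation .3 to .7 between months and 0 to .5 between substances (all assumed):

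- 4 tests: 14.7% to 18.1%;
- 8 tests, with initiation and escalation independent because they concern different participants: 27.5% to 33.1%.

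If all pairs share one correlation of .3, .5 or .7, 8 tests give 30.0%, 25.0% or 19.2%, and 2 tests give 9.5%, 9.0% or 8.4%.

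**Covariates.** SAP 6.1 adjusts for demographics, which the protocol's measures table lists as age, grade and gender. The 2020 update adjusts for baseline characteristics without listing them. Of the three factors behind the randomisation strata, only site appears in no covariate description.

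**The case against.** The strongest reply is that the dated updates govern. SAP 1.0 says the document captures updates to the analysis planning. The 2019 and 2020 entries are headed as updates to section 6.0, and together they give one outcome and one model. SAP 2.2.3 describes an intervention about alcohol, and the 2023 exploratory entry also works with past 3-month drinking days. This is the most natural reading, and it stands as far as it goes. It leaves three gaps: no sentence says that the updates replace 6.1 or 6.2; 6.2 was itself revised yet kept the older outcomes; and the mixed model names no deciding contrast.

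A reader might infer that the false-positive risk is about 30% instead of a promised 5%. The documents do not support that. The SAP never promises a family-wise 5%. A figure near 30% needs the eight-test count of the body text together with assumed correlations. A reader might also infer that both models are tested at two months, but only the logistic models are split by month.

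The marijuana point cannot be used twice. If the body governs, marijuana is tested and adds to the count. If the updates govern, its hypothesis in 2.1.1 has no primary test, and it does not add to the count.

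Nor can it be inferred that all the stratification factors are left out of the models, since 6.1 covers age and gender through demographics.

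**Conclusion.** The point holds as a failure of specification. The SAP carries two primary outcomes and two modelling approaches, names no deciding contrast and has no multiplicity rule. The chance of at least one false primary claim is 5% if the updates govern with one test, and at most 9.75% if 6 and 12 months are each tested. If the body text governs and the tests are independent, it is about 18% (4 tests) to 34% (8 tests); correlation lowers this somewhat. No single value in that range can be called the trial's error rate. The spread follows from the unreconciled text, and reconciling it matters whichever value applies. The figures assume two-sided tests at .05 with no true effect; the test counts are readings of the text, and the correlations are assumed.

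**What to change.** - In 6.1, 6.2 and 8.0, state that the 2019 outcome and the 2020 mixed model replace the earlier primary outcome and the separate logistic models.
- Name one deciding treatment contrast at two-sided .05, for example the arm difference at 12 months or the overall effect to 12 months. The documents do not settle this choice, so the SAP must.
- List the covariates and include the randomisation strata, in particular site.
- List initiation, escalation, marijuana and other time-point results as named secondary outcomes, all reported, either with a stated testing order or adjustment, or without confirmatory claims.
- Restate 9.0 for the outcome that is actually primary, with sidedness.

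The cost is SAP wording and a new power statement. The downside is that the older outcomes and the other time point can no longer be claimed as primary at an unadjusted .05.

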### **6.3 Definition of the Secondary Outcome Measures (Reference: Protocol p. 13- 21)**

We will also evaluate how well the change of intermediary measures predicts the change of substances use. We will use multiple logistic regression incorporating all intermediary variables. Separate models will be used to assess the associations at 6- and 12-month. We hypothesize that the following questions may serve as intermediary measures to predict long term substance use outcomes.

#### **Intermediary Measures**

##### **Knowledge about the impact of marijuana and alcohol on health**

Brief interventions to prevent or reduce adolescent substance use often focuses on increasing youth knowledge of the harms associated with use, with the expectation that increased knowledge will lead to decreased use over time. We will ask novel questions to assess participants' knowledge on the effects of substance use.

##### **Perceived risk of harm from substance use**

In nationally representative surveys, perceived risk of harm related to substance use is strongly associated with marijuana use on a population level, though less is known about the predictive validity on an individual level. We will ask participants questions regarding perceived risk of harm of alcohol, marijuana, tobacco and prescription medications in order to describe associations between perceived risk of harm and substance use trajectories.

### **Perceived availability of alcohol and marijuana**

Increased availability of alcohol has been associated with increased alcohol use and related problems in youth. To look at perceived availability of substances and the correlation with substance use on an individual level, we will ask a question about how difficult it would be for participants to get alcohol and marijuana if they wanted some. These questions were taken from the Monitoring the Future study.

### **Perceived likelihood of future substance use**

We will use questions from Monitoring the Future that ask about likelihood of future use validated in a longitudinal sample to determine whether this question is a good proxy measure of future use. We will ask participant about their likelihood of substance use three months from when they are completing the assessment battery and analyze responses against reports of actual substance use collected longitudinally.

### **Receipt of healthcare advice about substances from a medical professional**

To determine adolescents' experience of physician screening we will whether a clinician has asked about substance use and willingness to talk to a clinician or learn more about how alcohol use can affect health. We will use questions that were piloted by the research team in a previous project.

### **Confidence in refusal skills**

We are interested in learning about participant's confidence in their ability to refuse substances from friends. An adolescent's peers can have an influence on their behavior or substance use. We will include one novel question in our battery to assess participant's perceived self-efficacy.

### **Grit**

Perseverance and passion for long term goals may predict substance use trajectories. We will be administering the 8-Item Grit Scale, which is a two factor model that measures consistency of interest and perseverance of effort. The Grit Scale has been used in research settings and has been validated in both adult and adolescent populations. In these populations it has been used to look at relationships in educational attainment, career changes, and predicted populations. We will include all 8 items from the Short Grit Scale in our assessment battery.

### **Future goals for after high school**

Goals for the future may predict substance use by high school students. This has been studied in adjudicated adolescents, where positive future orientation was associated with lower levels of substance use. There has been little research in goal setting and future orientation as a predictor for other populations of adolescents. We would like to include a section on future goals in our assessment battery to study it further as a predictor for substance use. We will ask participants whether they have plans for their future after high school.

### Substance Specific Patient Centered Outcomes.

### **Problems and consequences associated with alcohol and marijuana use**

Standard measures of consequences related to substance use typically mix all substances together, creating a composite scale. For this project, we will separately determine the most common consequences reported by adolescents associated with alcohol use and marijuana use. Using the Personal Experience Screening Questionnaire (PESQ), we will ask participants substance specific outcome questions to determine whether alcohol and marijuana have different patterns of outcomes.

### **Sexual risk associated with substance use**

Risky sexual contact is commonly associated with alcohol use. Using questions adapted from the Youth Risk Behavior Survey, we will assess if a participant has ever engaged in sexual contact. Specifically, we are interested in whether there are different relationships and perceived concerns between alcohol and/or marijuana and unprotected sex.

### **6.4 Analyses of the Secondary Outcome Measures (Reference: Protocol p. 21)**

We will also evaluate how well the change of intermediary measures predicts the change of substances use. We will use multiple logistic regression incorporating all intermediary variables. Separate models will be used to assess the associations at 6- and 12-month.

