### **Description of Study Treatments or Exposures/Predictors**

This is a randomized control trial. We are interested in seeing if a brief electronic intervention that provides disease-specific information related to substance use as well as psycho-education on physical and mental well-being will have an impact on future substance use behaviors, knowledge, and perceptions.

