#### Secondary Outcomes (Reference: Protocol p. 21)

The brief intervention will target perceived risk of harm of a given substance, knowledge about substances, knowledge of disease specific and medication interactions, and intentions to use. These intermediary measures may serve as proxy markers that can be tracked and may predict substance use trajectories during a long term follow up period.

We evaluate how well the change of intermediary measures predicts the change of substances use. We will use multiple logistic regression incorporating all intermediary variables. Separate models will be used to assess the associations at 6- and 12-month.

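### No between-arm analysis is specified for any secondary outcome, and the models in SAP 6.4 leave lag and scoring undefined, so they cannot show that the intermediary measures predict use

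*Supplement*

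**What the plan says.** Protocol section D (Description of Study Treatments or Exposures/Predictors) sets the trial question as whether the electronic intervention "will have an impact on future substance use behaviors, knowledge, and perceptions".

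SAP 2.1.1, under Secondary Outcomes, takes this up: "The brief intervention will target perceived risk of harm of a given substance, knowledge about substances". Intentions to use, and knowledge of how substances interact with the disease and its medications, are named as further targets. The SAP describes all of these as possible proxy markers for later use. SAP 6.3 lists eight intermediary measures (knowledge, perceived harm, availability, likelihood of use, receipt of advice, refusal confidence, grit, future goals) and two patient-centred outcomes.

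The analysis is in SAP 6.4, with the same text in protocol section H. Its aim is to see how far change in the intermediary measures foretells change in use. The method is given as "We will use multiple logistic regression incorporating all intermediary variables". The 6-month and 12-month visits get a model each, and no lag between the two changes is stated.

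The arm comparison is written for use alone. SAP 6.1 reads "To evaluate the effect of intervention on substance use at 6- and 12-month follow-up, we will perform multivariate logistic regression". SAP 6.2 and the December 2020 update in section 11 plan a mixed model for alcohol use. Table A says only that the secondary outcomes will have a regression analysis.

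**The concern.** Two of the three things the protocol says the intervention may change, knowledge and perceptions, have no planned treatment-effect analysis. If alcohol use does not differ between arms, the plan cannot say whether the intervention failed to move its targets or moved them without changing behaviour. If alcohol use does differ, the plan offers no randomised evidence that the intended mechanism was engaged.

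The analysis that is planned does not fill this gap. It relates one change to another across all participants, with no arm term. The wish to treat these measures as proxy markers depends on their changing before use changes, and SAP 6.4 does not require that order. It also puts all intermediary variables into one model at each visit without saying how they are scored or how many terms result.

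**Working it through.** **1. Is there an arm contrast for any secondary measure?**

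| Place | Outcome compared between arms |
|---|---|
| Protocol H; SAP 2.1.1 and 6.1 | substance use |
| SAP 6.2 | alcohol use (mixed model); initiation and escalation of use |
| SAP 6.3 and 6.4 | none |
| SAP 11, 2016 | none (stratified randomisation) |
| SAP 11, 2019 and 2020 | alcohol use |
| SAP 11, 2023 | drinking days, post hoc, by baseline risk |

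No knowledge, perceived-harm or intention measure appears.

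**2. Can 6.4 show prediction?** The timeline calendar covers the past 90 days (SAP 2.2.5), and the 2019 primary outcome covers the past 3 months. Perceptions and knowledge are asked at the visit. If both changes run from baseline to the same visit, the use being predicted comes before the perceptions used to predict it.

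A lagged model fits the schedule. The protocol's contact windows are 5–8 and 11–14 months. The earliest 12-month assessment, at month 11, recalls use from 11 − 3 = month 8, which is when the 6-month window closes.

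**3. How many events per variable?** The plan gives no figure for the secondary analysis. Its only power statement (.80 with 300 completers and odds ratio 2.0) concerns initiation or escalation of use, and is used here only for its inputs.

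Inputs from the documents: 300 completers; odds ratio 2.0; intervention-group rate .20 to .55; past-year use among high-school youth in the preliminary study of 36.5% (alcohol) and 20.6% (marijuana). Assumptions: 1:1 allocation, the preliminary rates carried over to the completers, and the same .20–.55 range within each subset.

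- Control rate = 2o/(1 + 2o), with o = p/(1 − p). For p = .20: .50/1.50 = .333. For p = .55: 2.444/3.444 = .710.
- Overall rate = mean of the arms: .267 and .630.
- Limiting count = the smaller of events and non-events. For all 300: 300 × .267 = 80, and 300 × (1 − .630) = 111.
- Drinkers: 300 × .365 = about 109, giving 29 and 41. Marijuana users: 300 × .206 = about 62, giving 16 and 23.

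Items in the protocol's battery table for the eight domains: 9 + 10 + 3 + 4 + 4 + 1 + 8 + 1 = 40. With grit as one total score: 40 − 8 + 1 = 33.

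| Denominator | 8 domain scores | 33 terms | 40 items |
|---|---|---|---|
| All 300 | 10.0 and 13.9 | 2.4 and 3.4 | 2.0 and 2.8 |
| Drinkers | 3.7 and 5.1 | 0.9 and 1.2 | 0.7 and 1.0 |
| Marijuana users | 2.1 and 2.9 | 0.5 and 0.7 | 0.4 and 0.6 |

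Each pair is for intervention rates .20 and .55. These are the ends of the range, not its bounds: the limiting count is larger where the overall rate is near one half. At p = .40 the overall rate is .486, and the figures for 8 scores are 300 × .486/8 = 18.2, then 6.7 for drinkers and 3.8 for marijuana users. For 40 items in all 300 the figure is 3.6.

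For scale, in a simulation with independent, useless predictors and an event rate of .27 (200 runs), the mean apparent AUC was 0.60 with 8 scores and n = 300, 0.73 with 40 items and n = 300, 0.67 with 8 scores and n = 110, and 0.92 with 40 items and n = 110.

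**4. Is the missing contrast feasible?** With 150 per arm, the smallest difference detectable with 80% power is (z for alpha + 0.842) × √(2/150).

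- Two-sided .05: (1.960 + 0.842) × 0.1155 = 0.32 SD.
- Three targets at two visits, Bonferroni .05/6: (2.638 + 0.842) × 0.1155 = 0.40 SD.
- All eight measures at two visits, Bonferroni .05/16: (2.955 + 0.842) × 0.1155 = 0.44 SD.

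Without correction, the familywise error for independent tests is 1 − .95⁶ = .26 for six tests and 1 − .95¹⁶ = .56 for sixteen.

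**The case against.** The stated hypotheses concern use only, so the absence of an arm contrast could be deliberate. That weakens the point but does not remove it: the protocol names knowledge and perceptions in its trial question, and the SAP places the targets under a Secondary Outcomes heading.

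A reader might infer that 6.4 is the only analysis touching these measures, and that it is a single same-visit model. The documents do not support that. Separate models are planned for the two visits. SAP 6.3 also plans to set perceived likelihood of use against later reported use, and SAP 6.1 plans associations of predictors with use. Concurrency is the natural reading of 6.4 but is not written there. None of these analyses compares arms on a secondary measure.

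The SAP also words its aim cautiously ("We hypothesize that the following questions may serve as intermediary measures to predict long term substance use outcomes") and makes no claim of mediation. That is fair, but even a modest claim of prediction needs the predictor to come first.

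A reader might further infer that the models are overfitted as a matter of fact. That is not established. SAP 6.4 does not confine the model to drinkers or marijuana users, the 2019 alcohol outcome has no such restriction, and the protocol intends a total score for grit. The item count comes from the battery table shown. The follow-up battery is abbreviated and not shown, and the assessments were revised in 2017, so the true number of change variables is unknown.

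**Conclusion.** The concern holds in a limited form. No between-arm analysis of any secondary measure is specified, so a question the protocol poses goes unanswered if the plan is followed. This rests on the text alone. The 6.4 models, read naturally as concurrent, cannot show that change in these measures comes before change in use.

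Overfitting depends on choices the SAP leaves open. It is borderline to acceptable with eight domain scores in all completers (10 to 14 events per variable at the ends of the rate range, about 18 mid-range). It is a serious risk among drinkers (about 4 to 5, under 7 mid-range), among marijuana users (about 2 to 3, under 4 mid-range), and at item level (below 3 at the ends, below 4 mid-range, with 40 items). These figures rest on the allocation, use rates and event rates assumed above.

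The primary alcohol comparison is unaffected. This should be corrected, but it does not threaten the main result.

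**What to change.** Amend SAP 6.4 by a dated entry in section 11:

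- **Arm comparison.** Compare arms on knowledge, perceived harm and intention to use, each as a defined scale score, with the mixed-model structure already planned for alcohol use, baseline adjustment and a stated multiplicity rule. Holm is one suitable choice. Label the analysis post hoc if it is added after outcome data have been seen by arm.
- **Prediction.** Use baseline-to-6-month change in the domain scores to predict 12-month use, adjusting for 6-month use and arm. Report any concurrent model as an association only.
- **Terms.** Enter domain scores, with grit as its total, instead of individual items, and state the denominator for each model.

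The data are already planned, so the cost is analysis time and SAP text. Scoring rules must be written for the novel items, including the knowledge questions, which is more than a wording change. Participants who miss a follow-up drop out of the lagged model unless their data are imputed.
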